### Participant discontinuation and withdrawal

Patients who are withdrawn from the trial protocol will be followed up and analyzed as the remaining patients (intention-to-treat analysis, ITT).

### Suspension of the protocol

The protocol may temporarily be suspended for the individual patient, at the discretion of the treating clinicians, if the patient is to be resuscitated in the presence of any acute condition superimposed on septic shock, as judged by the investigator. Patients to be operated on at operational theatres may also have their procedures suspended during that time.

### Severe adverse reactions (SARs)

SARs to norepinephrine:Cerebral hemorrhage seen on computed tomography (CT) or magnetic resonance imaging (MRI) scanCardiac arrhythmia resulting in the use of medication or electrical cardioversionPsychiatric symptoms resulting in the use of antipsychotic drugs

Not registered as SARs to norepinephrine: tremor, headache, dizziness, and sweats are not registered. Hypertension is not registered. Dyspnea itself is not regarded as a serious adverse event (SAE). Hypersalivation, nausea, and vomiting are not registered.

SAEs will not be recorded as an entity, because the majority of septic ICU patients will experience several SAEs during their critical illness. The most important SAEs will be captured in the secondary outcome measures and in the daily Sequential Organ Failure Assessment (SOFA)-scoring. Patient charts will contain daily registrations of detailed clinical data, which can be obtained on request from the medical authorities. Trial investigators are to report suspected unexpected serious adverse reactions (SUSARs) without undue delay to the chief investigators, which in turn will report these to the Swiss, Finnish and Danish Health and Medicine Authorities within 7 days after the report has been received.

### Statistical plan and data analysis

#### Sample size and power

We assume 25 % mortality in both study groups, and this phase II trial will be unlikely to have the power to detect any mortality difference between the intervention groups. Therefore, a surrogate endpoint (days alive in 30 days with normal lactate and without vasopressors) combining survival, need for vasopressor therapy, and normalization of hyperlactatemia has been chosen. A post-hoc analysis from the FINNAKI study in a similar study population revealed a 30-day mortality rate of 25 %, and in 98 patients (of 128) who survived the mean time alive without vasopressors or hyperlactatemia within 30 days (720 h) was 650 h (SD 35) (unpublished data).

In the power analysis we assumed that the time with vasopressors or hyperlactatemia among the 30-day survivors follow a log-normal distribution with mean of 70 h (70 minus “treatment effect among survivors for the TTP group”) and SD 30, this simulated value was subtracted from 720 h (the number of hours in 30 days). For each configuration of sample size, mortality rate and expected treatment effect we simulated data and compared the two groups using a Mann-Whitney test. Ten thousand simulations were done for each configuration to compute the power. The required sample sizes (both groups combined) to achieve 80 % power as a function of mortality proportion (i.e., fraction of patients with a zero value for the primary endpoint) and average change in the primary endpoint among survivors are displayed in Table 1.

**Table 1 Tab1:** Power calculations

	Change among survivors in hours (and among all patients)		
Mortality proportion	12 h (9 h)	18 h (13.5 h)	24 h (18 h)
20 %	340	156	90
25 %	438	194	118
30 %	562	270	158
35 %	660	348	210
40 %	660	456	282

The clinically relevant difference in the study primary outcome to be tested is 18 h (Amendment 1 to the study protocol – 26 October 2015). An adaptive sample size adjustment will be employed. After 150 patients have been included and followed for 30 days, the study statistician (Assoc. Professor [name], University of Copenhagen) will redo the power calculation based on the observed mortality proportion and the observed dispersion in the primary outcome. The calculation will be done without un-blinding the study and will follow the previous recommendation by Chow and Chang (based on the revised power calculation a suggestion for a revised sample size will be presented to the investigators) (https://www.crcpress.com/Adaptive-Design-Methods-in-Clinical-Trials-Second-Edition/Chow-Chang/9781439839874).

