**Methods/design:**

The targeted tissue perfusion versus macrocirculation-guided standard care in patients with septic shock (TARTARE-2S) trial is a prospective, two-parallel-group, randomized, open-label, multicenter trial with assessor-blinded outcome evaluation. We will randomize at least 200 patients with septic shock in four European intensive care units (ICUs) to test whether a tissue perfusion-guided treatment strategy based on capillary refill time, peripheral temperature, arterial lactate concentrations, and accepting lower MAP levels, leads to a faster resolution of shock than macrocirculation target-guided standard care.

The primary outcome measure is days alive in 30 days with normal arterial blood lactate (first value of <2 mmol/L) and without any inotropic or vasopressor agent. Secondary outcomes include individual components of the primary outcome, days alive without renal replacement, days alive without mechanical ventilation in 30 days, and new acute kidney injury. The sample size enables detection of a 13.5-h difference in the primary outcome with a type 1 error of 5 % and power of 80 %, assuming 25 % mortality and a mean of 650 h (SD 30) among the 30-day survivors. After 150 included patients the statistician masked for allocation group will recalculate the sample size potentially increasing the sample up to 300. The Data Safety and Monitoring Board (DSMB) will review the safety data after 100 patients.

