### Statistical methods

The study flowchart is included as Fig. 1. A Mann-Whitney test for differences in continuous outcomes including the primary outcome measure, and Fisher’s exact test for dichotomous variables will be done as a primary analysis. A sensitivity analysis in subgroups of patients with and without previous hypertension will be performed. The components of the primary outcome measure (time to normalization of lactate, time to stopping of all vasoactive drugs, and day-30 mortality) are all included among secondary outcomes. In all tests a *p* value of less than 0.05 will be considered statistically significant. If missing data are >5 %, multiple imputations will be performed. A detailed statistical analysis plan is provided in Appendix 5.

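### The 80 % power claimed for 200 patients rests on SD 30, while the plan's only source data give SD 35; with SD 35 the power is about 73-74 % before re-estimation, and two Table 1 cells also miss 80 %

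*Protocol article*

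**What the plan says.** All of this stands in the Protocol article.

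- **Source data** (Sample size and power, first paragraph). An unpublished post-hoc analysis of the FINNAKI study gave a 30-day mortality of 25 %. Among the 98 of 128 patients who "survived the mean time alive without vasopressors or hyperlactatemia within 30 days (720 h) was 650 h (SD 35" h).
- **Simulation model** (same section, second paragraph). The plan assumes that "the time with vasopressors or hyperlactatemia among the 30-day survivors follow a log-normal distribution with mean of 70 h" in the control arm, with the treatment effect taken off that mean in the tissue-perfusion arm, "and SD 30, this simulated value was subtracted from 720 h". On deaths: "We assume 25 % mortality in both study groups"; a death scores zero. The groups are compared by a Mann-Whitney test over 10,000 simulations per configuration.
- **Abstract, Methods/design.** A 13.5-h difference is said to be detectable with 80 % power, "assuming 25 % mortality and a mean of 650 h (SD 30) among the 30-day survivors". At least 200 patients are planned, with a possible increase up to 300.
- **Table 1** is introduced as "The required sample sizes (both groups combined) to achieve 80 % power as a function of mortality proportion" and change among survivors. The entry for 25 % mortality and 18 h is 194. The 12-h column shows 660 at both 35 % and 40 % mortality.
- **Re-estimation** (paragraph after Table 1). Once 150 patients have been followed for 30 days, the power calculation is repeated, blinded, with the observed mortality and dispersion. The revised size goes to the investigators as a suggestion.

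**The concern.** Time with shock is 720 h minus time without it, so both have the same SD. The source's 35 and the simulation's 30 are therefore two values for one quantity. The mean carries over exactly (720 − 650 = 70 h), but the SD drops by 5 h with no explanation. A smaller SD makes an 18-h difference easier to detect, so the unexplained change favours the headline power claim.

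Table 1 has a separate fault. For a fixed effect the required size must rise with mortality, because more patients are tied at zero and fewer carry information on the treatment effect. It rises in every other step of the table, so the same 660 cannot be the 80 % size at both 35 % and 40 % mortality.

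At stake are whether readers can rely on the 80 % stated for 200 patients, and whether they can use Table 1 as printed.

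**Working it through.** **Inputs.** Control mean 70 h; tissue-perfusion mean 70 − 18 = 52 h; SD 30 (simulation, abstract) or 35 (source); mortality 25 %; Mann-Whitney test at 0.05 (Sample size and power; Statistical methods). Assumed, because not stated: two-sided test, 1:1 allocation, the same SD in both arms, and deaths drawn at random for each patient. On all patients, 18 h among survivors is 0.75 × 18 = 13.5 h, which matches the abstract.

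**Model.** A log-normal with mean *m* and SD *s* has log-variance σ² = ln(1 + (s/m)²) and log-mean μ = ln(m) − σ²/2.

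| SD | Control (m = 70) | Tissue perfusion (m = 52) |
|---|---|---|
| 30 | σ² = ln(1.1837) = 0.169, μ = 4.164 | σ² = ln(1.3328) = 0.287, μ = 3.808 |
| 35 | σ² = ln(1.2500) = 0.223, μ = 4.137 | σ² = ln(1.4530) = 0.374, μ = 3.764 |

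The chance that a surviving tissue-perfusion patient has less shock time than a surviving control patient is Φ((μ_C − μ_T)/√(σ²_C + σ²_T)):

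- SD 30: Φ(0.357/0.675) = 0.70
- SD 35: Φ(0.373/0.773) = 0.69

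The Mann-Whitney test works on the distance of this probability from 0.5. That distance falls from 0.201 to 0.185.

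**Step 1: reproduce the plan (SD 30).** Power was simulated with deaths set to zero and a tie-corrected Mann-Whitney test, with 10,000 or more runs per cell. At 25 % mortality and 18 h, N = 194 gives 79 % and N = 200 gives 80 %. Thirteen of the 15 Table 1 cells fall at about 79-81 %. SD 30 was therefore really used and is not a misprint. Other readings of the model (equal coefficient of variation, pure shift, fixed numbers of deaths) do not reproduce the table.

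**Step 2: change only the SD to 35 (18 h).**

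| N | Mortality | Power |
|---|---|---|
| 194 | 25 % | 72 % |
| 200 | 25 % | 73-74 % |
| 236-240 | 25 % | 80-81 % |
| 300 | 25 % | 88-89 % |
| 200 | 30/128 = 23.4 % | 76 % |

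At 25 % mortality the shortfall at 200 is about 6-7 points, and about 40 more patients (40/200 = 20 %) are needed for 80 %.

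**Step 3: the two 660 cells (SD 30, 12 h).**

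| Mortality | Power at 660 | N for 80 % |
|---|---|---|
| 35 % | about 75 % | about 760 |
| 40 % | about 62 % | about 1,010 |

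**The case against.** **The design already adapts to this input.** The re-estimation after 150 patients uses the observed dispersion, which is the quantity in question. If the SD is 35 and mortality 25 %, the roughly 240 patients needed lie well below 300. A reader might infer that the trial will finish with 74 % power; the documents do not support that, because the figure describes 200 patients without the adaptive step. What remains is that the revised size is only suggested to the investigators, and that the 80 % is claimed for the initial size.

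**The SD difference is within sampling error.** For 98 survivors drawn from the plan's log-normal, the sample SD has a 95 % range of about 24-37 h if the true SD is 30, and about 27-45 h if it is 35. SD 30 is thus compatible with the source. This stands: 74 % is a conditional figure, not a demonstrated deficit. But the observed SD is the only estimate the plan offers, and it was replaced by a more favourable one without comment. A sentence giving a reason for SD 30 would explain the choice; it would not make 80 % follow from the cited data.

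**The SD is not the only departure from the source.** Mortality in the source is 30/128 = 23.4 %, and the plan uses 25 %, which is conservative. With both source values the power at 200 is about 76 %, so the shortfall is about 4 points.

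**The 660 cells change no decision.** They belong to the 12-h column, whereas the difference to be tested is set at 18 h, and 660, 760 and 1,010 all exceed the cap of 300. This also stands. It would be wrong to infer that these cells undermine the planned size; they are errors in a published table and nothing more. The repeated value may be the upper limit of a search grid, but the article does not say so.

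**Conclusion.** The point holds in a limited form. The 80 % power stated for 200 patients does not follow from the plan's own source data. With the source's SD of 35 it is about 73-74 % at 25 % mortality and about 76 % at 23.4 %, before any re-estimation, and about 240 patients are needed for 80 %. The planned re-estimation can close this gap within the cap at 25 % mortality. The fault is therefore an overstated initial justification, not a design that must end underpowered. Nor do the documents show why 30 replaced 35, so no motive should be read into it.

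Two Table 1 cells are wrong as printed, with about 75 % and 62 % power in place of 80 %, and have no bearing on the planned size.

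The figures assume a two-sided test, 1:1 allocation, equal SDs in the two arms and randomly drawn deaths. This is the reading that reproduces the rest of Table 1.

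**What to change.** 1. Rerun Table 1 with SD 35.
2. Restate the abstract and the sample size section: with SD 35, 25 % mortality and an 18-h difference among survivors, 200 patients give about 74 % power and about 240 give 80 %, subject to the blinded re-estimation after 150 patients and the cap of 300.
3. Correct the two 660 entries. If the SD 30 table is retained for reference, they become about 760 (35 % mortality) and about 1,010 (40 %), or both are marked as above 660.

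The cost is one rerun of an existing simulation and a few edited figures. The test, the significance level, the re-estimation and the cap stay as they are, and the correction does not itself require more patients.

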### Statistical methods

The study flowchart is included as Fig. 1. A Mann-Whitney test for differences in continuous outcomes including the primary outcome measure, and Fisher’s exact test for dichotomous variables will be done as a primary analysis. A sensitivity analysis in subgroups of patients with and without previous hypertension will be performed. The components of the primary outcome measure (time to normalization of lactate, time to stopping of all vasoactive drugs, and day-30 mortality) are all included among secondary outcomes. In all tests a *p* value of less than 0.05 will be considered statistically significant. If missing data are >5 %, multiple imputations will be performed. A detailed statistical analysis plan is provided in Appendix 5.

**Fig. 1 Fig1:**
[figure not shown]
The TARTARE-2S study flowchart

### Interim analysis

As this trial is a feasibility trial we do not consider an interim analysis appropriate. As an interim analysis will not be performed, statistical early stopping criteria will not be applied. However, the Data Safety and Monitoring Board (DSMB) has full access to the safety data and will do a thorough review of these after 100 patients, and may recommend stopping the study anytime based on safety concerns.

### Intervention accountability

Every patient will be allocated a registration sheet to be kept in the site master file. The initials, birth date, screening number, time for randomization, and study arm will be included. The compliance of trial arm targets for each study patient will be checked hourly for the first 72 h, and clinical problems and given hemodynamic treatments will be registered until the study combined endpoint has been fulfilled, up to day 30. The originals for these documents will be kept as the study source data at each site.

### Registration

ClinicalTrials.gov: NCT02579525 (Registration date 19 October 2015).

### Data to be registered

The continuous data on hemodynamic parameters will be registered as 10-min medians using electronic PMDS, when possible and otherwise registered each hour to 72 h. For other data please see “Appendix 4.” The Standard Protocol Items: Recommendations for Interventional Trials (SPIRIT) figure regarding study interventions and timing is provided as Fig. 2.

**Fig. 2 Fig2:**
[figure not shown]
The schedule of enrollment, interventions, and assessments

### Data handling

Data will be entered into an electronic, web-based electronic Case Report Form (eCRF) from patient notes by trial personnel. Each patient will receive a unique trial identification number. Trial investigators will receive a personal username and passwords to access the TARTARE-2S trial web-page. Each site will only have access to site-specific data. Data will be handled according to the Swiss, Finnish and Danish laws. All original records (including Informed Consent Forms, eCRFs, and relevant correspondences) will be archived at trial sites for 15 years. The clean electronic trial database file will be delivered to the Inselspital Data Archive and maintained for 15 years and anonymized, if requested by the authorities.

### Monitoring

The trial will be externally monitored (Clinical Trial Unit, Bern) to Good Clinical Practice (GCP) standards. A centralized day-to-day monitoring of the eCRF will be done by the coordinating investigator.

### Ethical considerations

In addition to fluid therapy, norepinephrine administration to increase the MAP is a key element in the treatment of septic shock. As the intervention is very frequent, but not evidence-based and carries potential risks, we consider it to be in the wider interests of society and patients to perform research in this area, as clearly highlighted in a recent systematic review and meta-analysis [9]. The present trial is a phase II trial, i.e., a trial assessing both the feasibility of the protocol in a clinical setting and a patient-centered surrogate outcome. Should the trial prove feasible with separation between the two interventions, and suggest a benefit in terms of the primary endpoint, a larger phase III trial assessing 90-day mortality is intended. Thus, it is the opinion of the Steering Committee that this study is very important and ethically justified.

In some retrospective observational studies, low MAP has been associated with an increased risk of acute kidney injury (AKI) [22–24]. However, causal inferences cannot be drawn from observational data with the inherent limitation that the most severely ill patients inevitably have lower MAPs. In the present study: (1) a minimum safety limit of MAP has been set to the TTP group, (2) the study patients are carefully monitored and re-evaluated, and treatment goals are registered every hour. In addition, (3) the treating clinician should allow lower MAP values only in situations without any clinical problems, such as oliguria, in which cases individual use of higher MAP targets is allowed (and also in previously hypertensive patients). Thus, the Steering Committee has strong reasons to believe that the care of the study patients will be better and safer than the highly varying standard clinical practice; e.g., regarding fluid treatment [25]. In addition, high-quality randomized controlled trials (RCTs) focusing on unproven but widely used standard treatments have been shown to change clinical practice and to save future critically ill patients from untoward adverse events and death, e.g., by avoiding the use of starch in septic shock [26].

Treatment of septic shock is time-dependent and many patients will be unconscious and, due to fever and/or septic brain dysfunction, unable to consider an informed consent. Inclusion of only conscious less severely ill patients would cause a significant bias and jeopardize the study results. Furthermore, the treatment separation and effect are plausibly most obvious the earlier the randomization occurs. Of note, both treatment arms are within the frame of current standard clinical practice and no investigational drugs are used, thus, ethically allowing the potential use of a deferred consent. Therefore, patients will be included either with a deferred consent, or a proxy consent (next of kin) according to national laws in Finland, Switzerland, and Denmark (two-physician consent also allowed in Denmark). The patient or next of kin and/or general practitioner will be asked for a deferred consent if required by national law.

The trial will adhere to the trial protocol, the Helsinki Declaration in its latest form, GCP guidelines, and the national laws in the countries involved. Inclusion will start after approval by the ethics committees, medicines agencies, data protection agencies, and health authorities in the countries of the trial sites.

### Informed consent

The process leading to obtaining informed consent will be in compliance with all applicable regulations and national laws. Patients with septic shock are seldom able to consider their consent due to fever, mechanical ventilation, sedation, and/or septic encephalopathy. However, those patients who regain consciousness will be asked for informed consent as soon as possible. The possible benefit of the treatment (and the separation between the study arms) will plausibly be larger the sooner the treatment is started. In addition, it is important not to introduce a significant bias to the study results by only including less severely ill patients because most plausibly the most severely ill patients will benefit most. The consenting party will be provided with written and oral information about the trial so they are able to make an informed decision about participation in the trial. Written information and the consent form will be subjected to review and approval by the National Ethics Committee.

### Duration

For clinical treatment, primary and secondary endpoint up to 30 days; follow-up exploratory endpoint until day 90.

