### Secondary outcome measures

Time to normalization of lactateDays alive with normal lactate (all values <2 mmol/L) in 30 daysDays alive without the use of inotropic or vasopressor agents in 30 daysDays alive without RRT in 30 daysDays alive without mechanical ventilation in 30 daysDays alive without any organ support (mechanical ventilation, RRT) in 30 daysNew AKI according to the KDIGO classification (stages I–III)8.. Days alive outside hospital in 90 daysTotal amount of norepinephrine given until day 5Number/total number of the following adverse reactions:ventricular tachycardia/fibrillationatrial fibrillationmyocardial infarctionskin necrosisstrokesecondary bowel ischemialimb ischemiatotal numbers of serious adverse reactions (SAR) (numbers of patients and reactions)

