### Exploratory outcomes

All-cause mortality at day 90.

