### Blinding

Blinding of health care providers will not be feasible which infers that all clinical staff caring for the patients will be aware of the allocation during the intervention period. The two interventions may lead to different use of concomitant interventions, but the lack of blinding may also result in differences in the use of concomitant interventions during the intervention period. Hence, we will provide suggestions for the use of relevant co-interventions (see “Concomitant interventions”) and will record the use of them.

Information on the primary outcome and other secondary outcomes will be provided by the local investigators from patient charts, but the statistician doing the analyses will be blinded to which intervention the patients received. Information on whether the exploratory outcome of death occurs will be acquired through public registers (the National Civil Registries) without knowledge of which intervention group the patient was allocated to. In Switzerland, the patient or relatives will be contacted. The assessor of the outcomes will be blinded to the study group. The members of DSMB will remain blinded unless they request otherwise.

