## Appendix 4 Data to be registered

Data will be obtained in eCRFs from a combination of national registers and medical records. Bedside target list for treatment reasons and decisions will be implemented in the PDMS (*) at each site, if possible.

Baseline variables

- National identification number (if available)
- Sex
- Age at randomization
- Estimated height
- Measured (if not possible estimated) weight
- Comorbidities? Y/N (hypertension*, chronic heart failure*, previous myocardial infarction, previous stroke, chronic obstructive pulmonary disease*, diabetes*, hematological malignancy*, metastatic cancer*, AIDS*)
- Elective or emergency admission*
- Operative or non-operative admission*
- Site of infection (pulmonary/abdominal/urinary tract/soft tissue/other)
- Previous plasma/serum creatinine (7–365 days before hospital admission), if available

24-h from ICU admission:

- Values for Simplified Acute Physiology Score (SAPS II)*

Twenty-four hours before randomization

- Volume of resuscitation fluids (crystalloids, colloids and blood products specified in milliliters)
- Hemoglobin (lowest)*
- SOFA score *variables**

At randomization

- Norepinephrine dose and mean arterial pressure (MAP) at the same time
- Total fluids given in last 2 h
- Lactate (last value from the previous 2 h)

Continuously as 10-min medians in the first 72 h after randomization:

- Systolic arterial pressure*
- Mean arterial pressure*
- Central venous pressure*
- Heart rate*
- Peripheral oxygen saturation (SpO_2_)*
- Continuous central venous oxygen saturation, if available
- Continuous mixed venous saturation, if available
- Dose of norepinephrine*
- Dose of dobutamine*

One-hour intervals (for 72 h)

- Urinary output*
- Volume of given fluids
- CRT – only in the TTP group
- Assessment of upper arm temperature – only in the TTP group
- Assessment of skin mottling score – only in the TTP group

Two-hour intervals (for 72 h unless study endpoint reached)

- Arterial lactate measured in both groups

Four-hour intervals during the first 72 h after randomization (if not discharged from the ICU)

- Arterial blood gas tensions (PaO_2_, PaCO_2_), pH and base excess (BE)
- Calculated Mixed v-aCO_2_/Da-vO_2_-ratio (if pulmonary artery catheter, PAC)
- Cardiac index (if PAC)
- Stroke index (if PAC)

Daily in the first 7 days after randomization (if not discharged from the hospital):

- SOFA score variables*
- Total volume of fluids
- Estimated fluid balance

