- Dose of glucocorticoids (not recommended)

Daily up to 30 days:

- On mechanical invasive- or non-invasive ventilation? Y/N
- Ventilator settings at 8 a.m. (PEEP, Pplat, Vt)
- Use of muscle relaxants during the last 24 h? Y/N
- Presence of acute kidney injury (AKI) according to KDIGO classification? Y/N/and stage (I–III)
- Use of renal replacement therapy? Y/N
- Use of vasopressors? Y/N
- Use of inotropic agents? Y/N
- Ischemic events
- SARs and SUSARs

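### The Duration section ends secondary follow-up at day 30, but one secondary outcome runs to day 90, and the Timeline closes follow-up too early for any 90-day outcome

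*Protocol article*

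**What the plan says.** Four parts of the protocol article bear on the follow-up of secondary outcomes.

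- **Duration:** "primary and secondary endpoint up to 30 days; follow-up exploratory endpoint until day 90".
- **Outcomes:** The eighth secondary outcome is "Days alive outside hospital in 90" days. The Exploratory outcomes section has a single entry, "All-cause mortality at day 90". Appendix 5 refers to the secondary outcomes by letter and assigns outcome h, the eighth, an unadjusted Mann-Whitney test.
- **Timeline:** The last participant is enrolled in November 2017, follow-up is complete in December 2017, and analysis and submission of the main paper are set for March 2018.
- **Data sources:** The Blinding section states: "Information on the primary outcome and other secondary outcomes will be provided by the local investigators from patient charts". On vital status it states: "Information on whether the exploratory outcome of death occurs will be acquired through public registers"; in Switzerland the patient or relatives are contacted instead. Appendix 4 opens with "Data will be obtained in eCRFs from a combination of national registers and medical records". Its last block is headed "Daily up to 30 days" and covers ventilation, kidney injury, renal replacement, vasopressors, inotropes, ischemic events and adverse reactions.

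**The concern.** Days alive outside hospital is the only secondary outcome with a stated 90-day window, and the only one that describes recovery after the acute phase. The Duration section puts it in the class of endpoints that stop at day 30. The dated items in Appendix 4 stop at day 30 too, and the visible list has no discharge date, readmission or count of hospital days. The one day-90 source tied to a specific outcome concerns death, and knowing that a patient is alive does not show whether that patient is in hospital.

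A site that plans its work from the Duration section, the Timeline and Appendix 4 could reasonably stop secondary follow-up at day 30 while the statistician expects 90 days. The gap would fall on patients still in hospital at day 30 or readmitted later. If it pushed missing data for this outcome above 5 %, Appendix 5 would make multiple imputation the primary analysis for that test and would require every test to be run both ways.

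**Working it through.** No sample-size, power or alpha figure is involved. The check compares the stated windows and then does date arithmetic on the Timeline.

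**1. Windows side by side**

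| Item | Window | Place |
|---|---|---|
| Secondary endpoints, general rule | 30 days | Duration |
| Days alive outside hospital | 90 days | Secondary outcome measures; tested in Appendix 5 as outcome h |
| All-cause mortality | day 90 | Exploratory outcomes |
| Longest dated block in the data list | 30 days | Appendix 4 |

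The first two rows cannot both hold. The difference is 90 − 30 = 60 days that the Duration rule does not cover. This is the distance between two stated windows; it estimates neither missing data nor bias.

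**2. Timeline**

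Inputs: last enrolment some time in November 2017; follow-up complete by the end of December 2017. The Timeline gives months only, so 31 December is an assumption and the latest possible date.

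- 30-day window: 1 November + 30 days = 1 December 2017; 30 November + 30 days = 30 December 2017. Both fall within December.
- 90-day window: 1 November + 90 days = 30 January 2018; 30 November + 90 days = 28 February 2018. Both fall after the stated close.
- Shortfall for the last patient, counted from 31 December: 30 days if enrolled on 1 November and 59 days if enrolled on 30 November.
- Latest enrolment date with a full 90 days: 31 December − 90 days = 2 October 2017. A close earlier in December moves this date back day for day, to 2 September 2017 for a close on 1 December.

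The planned dates therefore fit a 30-day trial and not a 90-day one. The same shortfall applies to day-90 mortality, which every section that mentions it treats as planned.

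**3. What is and is not secured for the 90-day outcome**

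- Alive to day 90: planned, through registries or contact (Blinding).
- In or out of hospital, days 31 to 90: no section names a specific item or date. Charts and national registers are named as general sources, without a 30-day limit.

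**The case against.** The strongest reply is that one loose summary sentence should not override an outcome that is explicitly defined and has a planned test. Much of this stands.

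- **Sources exist.** Charts are named for secondary outcomes, and registers and medical records for the data list. None of these statements stops at day 30, and either source could supply hospital stays. Survival to day 90 is planned.
- **Appendix 4 is not exhaustive.** It also omits day-90 vital status, which the Blinding section plans to collect. It lists norepinephrine dose only for the first 72 h, although a secondary outcome totals norepinephrine to day 5. Some of its items are conditional on the patient still being in hospital, so discharge status is evidently known to the trial, at least early on.
- **The schedule of assessments (Fig. 2) was not available for this check.** A day-90 hospital-status entry could stand there, and an article may leave such fields to the full protocol or eCRF.

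Two stronger readings are tempting, and the documents do not support either. A reader might infer that the outcome cannot be computed because hospital days after day 30 are not collected; the points above show that this does not follow from a data list known to be incomplete. A reader might also infer that a patient in hospital throughout could be credited with up to 60 days outside it. That requires a rule counting unobserved days as days at home, and the plan states no such rule.

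The reply does not remove the contradiction itself. The Duration section does not merely omit this outcome; it assigns secondary endpoints to day 30 and reserves day 90 for another endpoint. That the Timeline is also too short for mortality does mean it is no evidence about hospital data in particular, but it makes the Timeline a second error to correct, not a reason to leave the first.

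**Conclusion.** The point holds as an internal contradiction about follow-up that puts one secondary outcome at risk. The Duration section and the definition of days alive outside hospital differ by 60 days. The Timeline closes 30 to 59 days too early for patients enrolled in November 2017 and gives a full 90 days only to those enrolled by 2 October 2017, assuming a close on 31 December.

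The primary outcome, the sample size, the power and the significance level are untouched. Whether any data would be lost depends on how sites read the conflicting sections and on what the eCRF and Fig. 2 contain, so the size of any bias, or any difference between arms, cannot be stated from this document. Nor is there a case for cutting the outcome to 30 days: it is clearly defined and has an analysis assigned, and the sections that disagree with it are the ones to amend.

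**What to change.** Three changes bring the text into line:

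1. **Duration:** state that days alive outside hospital is followed to day 90, together with the exploratory mortality endpoint, and that the 30-day limit applies to the other outcomes with a 30-day window.
2. **Timeline:** move completion of follow-up to at least 90 days after the last enrolment, which is 28 February 2018 for an enrolment on 30 November 2017.
3. **Appendix 4:** add hospital discharge and readmission dates to day 90, taken from charts or registers at the same time as the day-90 vital status, and list that vital status as an item too.

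The cost is a few eCRF fields, filled at a register query or contact that is already planned, and a follow-up end date about two months later. The March 2018 target for analysis and submission would then come directly after the end of follow-up and should be checked.
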